#### Plans to promote participant retention and complete follow-up {18b}

For all patient surveys and interview invitations, up to three contact attempts will be made to ensure the completion of surveys and/or interviews. For stakeholder and CP interviews and surveys, potential participants will be contacted up to three times to inquire about interview and survey participation.

#### Data management {19}

Data will be collected directly from the patient or from the Epic EHR system. REDCap will be used to log electronic data collected from the Epic EHR. REDCap is a HIPAA-compliant database that contains multiple levels of authentication and access controls. All changes to the data and each “record viewed” are logged back to the individual login ID with a timestamp. REDCap also has several built-in functions to control the exportation of identifying information.

Medical records will be abstracted electronically by approved research staff. Paper forms (if necessary) may also be uploaded as a PDF or manually entered into the REDCap system. All research material will be maintained on a secure server or locked in file cabinets. All material will be destroyed 7 years following the completion of the study. The research data are only accessible with password-protected and logged access to a secure server at Mayo Clinic. Other study data, e.g., interview data, will be stored in a secured server with restricted access only to the study staff. While qualitative data will not be made available on an open platform, published results will include a rich description that includes de-identified quotes from participants.

#### Confidentiality {27}

The privacy of all study participants will be protected by avoiding the use of names on all research data. All study participants will be identified by a unique study code number. The link between the code number and the study participant’s identity will be stored in a remote data capture (RDC) system that is password-protected and only accessible to study personnel, all of whom have human subject research training.

The potential risks of breached confidentiality will be minimized by ensuring that the data are private, only used by members of the research team, and only used for the specific purposes of this study.

#### Plans for collection, laboratory evaluation, and storage of biological specimens for genetic or molecular analysis in this trial/future use {33}

This trial does not involve the collection, laboratory evaluation, or storage of biological specimens for genetic or molecular analysis.

## Statistical methods

### Statistical methods for primary and secondary outcomes {20a}

#### Aim 1

We will use methods of rapid qualitative analysis, guided by constructs in the Consolidated Framework for Implementation Research (CFIR) [22]. Members of the study team will meet to review notes and audio recordings from interviews and discuss issues that may impact implementation, including those that should be addressed before trial enrollment commences. Notes will be summarized in a template guided by the CFIR framework and imported into qualitative software (NVivo, QSR International) for data management. Summaries will be presented at biweekly study team meetings for discussion of potential actions, including changes to the implementation plan.

#### Aim 2

The main analysis of the primary outcome will be based on the intention-to-treat (ITT) principle, with all patients randomized to CACP compared to all patients randomized to usual care. The ITT sample will comprise all patients who were randomized and completed the baseline assessment. The primary outcome (CACP effectiveness) is defined as the number of days the patient was alive and outside of the ED or hospital (excluding planned hospital admissions for scheduled surgeries, procedures, and/or treatments). Outcomes will also be analyzed in the per-protocol subset. The per-protocol sample will comprise all patients in the ITT arm except for those who did not follow protocol, i.e., patients who did not receive CP services in the intervention arm.

The mean number of days out of the ED or hospital for the intervention group will be compared to that of the control arm. Statistical significance, and a two-sided confidence interval for the difference between arms, will be assessed by using the two-sample *t* test. The distributional assumptions for the test will be assessed by calculating the skew and kurtosis for the bootstrap distribution of the sample difference between means. The Hodges-Lehman shift estimator for the Wilcoxon rank-sum test will be used if the absolute value of the skew or kurtosis-minus-three are greater than 1.5.

Other continuous outcome measures will be assessed by the same method as the primary outcome measure. Categorical measures will be assessed by using the Pearson chi-square test, or the Fisher exact test will be used if the minimum expected cell count is less than five.

Sensitivity analyses concerning the primary and secondary endpoints will be conducted, including excluding hospice deaths, examining the impact of the number of CP visits, examining the impact of the duration of CP care (< 10 days, 10–19 days, 20–29 days) and per protocol vs ITT. The impact of covariates will be assessed by using multiple linear regression or multiple logistic regression.

Descriptive statistics and figures will be provided as appropriate for secondary outcomes, and baseline demographics will be summarized for each arm. Validated instruments (e.g., EQ-5D) will be scored per official guidance, and the results will be reported as appropriate. When data is available, changes in rates or scores between baseline and 30 days will be reported for each arm along with comparisons between the groups. Implementation outcomes will be summarized using descriptive statistics.

#### Aim 3

Qualitative data will be analyzed following qualitative content analysis procedures, guided by the theoretical constructs employed in the study. Analysis will begin with at least two members of the study team reviewing audio files and transcripts. A coding framework will be developed, starting with a priori topics in the interview guide and constructs from theoretical frameworks like CFIR. Analytic memos will be used to summarize the findings, including any key differences by participant role.

Surveys will be analyzed using descriptive statistics and scoring guidance for validated instruments (e.g., CSAT). Integration of findings will involve a comparison of quantitative and qualitative findings by construct, e.g., survey and interview data on acceptability and sustainability.

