### Data collection and management

#### Plans for assessment and collection of outcomes {18a}

Participants randomized to CACP will have access to CP services ordered and overseen by the treating clinical team per the current standard of care. Thus, the clinical trial evaluates the CACP care delivery model rather than the clinical care that is provided to patients within it. Participants randomized to usual care will not have access to CP services and will continue with their care as planned by the treating clinician(s).

All participants will complete a baseline survey at the time of enrollment/consent and at 30 days. Participants randomized to CACP will also complete a survey after their last CP encounter. Paper copies of the baseline surveys will be completed at the time of enrollment or provided to the participant and returned by mail. In the CACP treatment arm, we will ask that baseline surveys be completed and returned before or during the first CP visit. In the usual care arm, for participants who did not complete their baseline survey at the time of enrollment, up to 3 reminder phone calls will be made by a member of the research team to participants who have not returned their survey by the end of week 1.

Participants randomized to the CACP treatment arm will also be asked to complete a survey after their last CP visit. This survey will be handed to the participant by the CP at their last visit with a pre-stamped envelope so it can be completely private and returned by mail or sealed and given to the CP for delivery. If participants need help completing the survey, the research team study coordinator will contact them by telephone and complete the survey with them. Patients in the intervention arm who are recruited and consent to participate in an interview will complete it by telephone with a trained member of the study team unaffiliated with intervention delivery. Interviews will be audio-recorded with permission and transcribed for analysis.

Patients in both arms will be asked to complete a paper survey at day 30, administered between days 30 and 40 (first attempt) and with all 3 contact attempts completed by day 90. If participants need help completing the survey, it can be done over the phone with the research team study coordinator.

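### The ITT sample is defined two ways: all randomised patients, and only those who also completed a baseline assessment that may come back after open-label allocation

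*Protocol article*

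**What the plan says.** Section {20a}, Aim 2, bases the main analysis of the primary outcome on the intention-to-treat principle, "with all patients randomized to CACP compared to all patients randomized to usual care". The next sentence defines the set differently: "The ITT sample will comprise all patients who were randomized and completed the baseline assessment". The per-protocol sample is then carved out of that ITT sample, so it inherits the same condition.

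Section {18a} describes the baseline survey. The default is completion at enrolment: "All participants will complete a baseline survey at the time of enrollment/consent and at 30 days". A later route is also allowed: "Paper copies of the baseline surveys will be completed at the time of enrollment or provided to the participant and returned by mail". The return instructions then differ by arm. For the intervention arm: "In the CACP treatment arm, we will ask that baseline surveys be completed and returned before or during the first CP visit". For usual care, those who did not complete it at enrolment get up to three reminder calls, aimed at "participants who have not returned their survey by the end of week 1".

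For the patient-reported scores, {20a} adds that, when data are available, "changes in rates or scores between baseline and 30 days will be reported for each arm along with comparisons between the groups".

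**The concern.** An ITT set should be fixed by randomisation alone. Here one sentence does that and the next adds a condition that a patient can meet or fail after allocation, with the arm known and the outcome clock running. A patient who is hospitalised or dies in the first days loses exactly the days that the primary outcome counts, and is plausibly less likely to return a paper survey. If that happens at different rates in the two arms, the comparison is no longer protected by randomisation.

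The condition also brings nothing to the primary outcome, which is read from the EHR and can be ascertained whether or not a survey exists. A secondary matter is that a survey completed after allocation may serve as the baseline for EQ-5D and PETS change scores.

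**Working it through.** **1. Can the condition act after randomisation?** The relevant sections, side by side:

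- Recruitment {15}, Aim 2: randomisation follows informed consent. No section makes survey completion a precondition.
- {18a}: the survey may be returned by mail, and the return instructions depend on the arm, so they can apply only once the arm is known.
- {17a}: participants and care teams are not blinded.
- {11a}: the outcome clock starts the day after randomisation.
- {20c}: the primary outcome comes from the EHR. Multiple imputation is reserved for missingness above 20%, so it would not bring back patients left out of the set by definition.

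So it can. Under the narrower definition, membership may be settled inside the 30-day outcome window.

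**2. Is the baseline assessment the survey?** The article does not define the term. The survey is the only baseline item that it describes patients completing. The others in Table 3 (age, sex, race, ethnicity, comorbidities, medications) are taken from the EHR. Table 3 places the social support, EQ-5D and PETS surveys at allocation. The reading is a strong inference, not a stated fact.

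**3. Precision.** Sample size {14} gives a 2-day difference, SD 5, two-sided 0.05, 80% power and 120 per group. By the normal approximation, n = 2 × (1.960 + 0.842)² × 5² / 2² = 98.1, so 99 per group (100 by the t test). The stated inputs therefore do not reproduce 120. That is a separate matter and nothing here rests on it. With 120 per group, power = Φ(2 / (5 × √(2/120)) − 1.96) = Φ(1.14) = 87%.

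The article gives no non-return rate. If an equal share of both arms were excluded (assumed values):

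| Excluded in each arm | Left per arm | Power |
|---|---|---|
| 5% | 114 | 86% |
| 10% | 108 | 84% |
| 15% | 102 | 82% |
| 17.5% | 99 | 80% |
| 20% | 96 | 79% |
| 30% | 84 | 74% |

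**4. Bias.** Let pC and pU be the excluded shares in CACP and usual care, and let D be the number of days by which excluded patients fall short of retained ones, taken as equal in both arms. In each arm, mean of all randomised = mean of retained − p × D. The difference among retained patients therefore equals the true difference plus D × (pC − pU).

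Assume pC = 5% and pU = 15%. Retained numbers are 120 × 0.95 = 114 and 120 × 0.85 = 102, and SE = 5 × √(1/114 + 1/102) = 0.68.

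| D (days) | Bias, CACP − usual care | Two-sided type I error | Power for a true 2 days |
|---|---|---|---|
| 3 | 3 × (−0.10) = −0.3 | 7% | 70% |
| 5 | 5 × (−0.10) = −0.5 | 11% | 60% |
| 10 | 10 × (−0.10) = −1.0 | 31% | 31% |

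With the shares swapped (15% and 5%), the biases are +0.3, +0.5 and +1.0 and favour CACP. The type I error is the same by symmetry. With equal shares and equal D, the bias is zero. Against the 2-day target, 0.3 to 1.0 day is 15% to 50%.

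**The case against.** The strongest reply is that the protocol commits itself to intention-to-treat: once in the sentence on all randomised patients, and again in {20c}. A reader might infer from the narrower sentence that the primary comparison is definitely not intention-to-treat. The text does not support that. It shows two incompatible definitions, not a settled choice of the wrong one.

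Other points that stand:

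- Completion at enrolment is the default and mailing is the alternative. Section {18b} promises up to three contact attempts for all patient surveys, so the contrast in follow-up between arms is softer than {18a} alone suggests. No cut-off for return is given, so a usual-care patient readmitted in week 1 may still be called and still be included.
- A reader might infer that patients with early hospital use will be lost, at different rates by arm, in a known direction. The article gives no non-return rate, no timing of the first CP visit and no profile of non-returners. This is a plausible risk, not a derived result.
- A reader might infer a serious loss of power. At the stated inputs, about 17.5% of each arm could be excluded before power falls to 80%, and 20% leaves 79%. The loss is minor.
- A reader might infer that every survey completed after allocation must be discarded as a baseline, or that the survey must be moved ahead of randomisation. Under Trial status, recruitment is already under way, so a procedural change cannot reach patients already randomised. Table 3 itself places these surveys at allocation, so discarding could remove many. Table 1 already lists a between-group comparison of EQ-5D and PETS at 30 days.

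None of this removes the contradiction, or gives a reason to tie an EHR outcome to a baseline assessment.

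**Conclusion.** The concern holds as an inconsistent definition of the primary population that should be resolved before analysis. Confidence is high on the contradiction. That the condition refers to the survey is a strong inference. That applying it would bias the result is a risk of unknown size and sign.

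The figure of 0.3 to 1.0 day in absolute value is an illustration. It assumes a 10-point difference between arms in the share excluded, a deficit of 3 to 10 days that is equal in both arms, and the plan's own SD of 5. The harm to guard against is bias rather than lost power. The change-score issue is real but secondary, because a comparison at 30 days is already planned.

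**What to change.** 1. In {20a}, remove the baseline-completion condition from the sentence that defines the ITT sample. Define the set as every randomised patient, analysed in the allocated arm, with the EHR outcome used whatever the survey status. The per-protocol set then derives from this corrected set.
2. Confine the baseline-survey requirement to the EQ-5D and PETS change analyses.
3. For those two measures, name the already planned comparison of 30-day scores between arms as the main one. Report change scores as supporting, with baselines completed after allocation flagged.

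The cost is small: a one-sentence change to the population and a short note on the patient-reported scores. It needs no new patients or visits, and it applies equally to patients already randomised. The flag needs the date on which each baseline survey was completed. The article does not say whether this is recorded; where it is not, the date of return would have to stand in. Under {25}, changes to analyses are communicated to the steering committee.

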Aim 2 will evaluate CACP effectiveness (compared to usual care) and implementation outcomes using mixed methods. The primary effectiveness outcome is the number of days alive out of ED or hospital within 30 days of the day following randomization, ascertained by EHR review; this outcome includes all unplanned hospitalizations, ED visits, and deaths, which will also be assessed separately as safety endpoints. This primary outcome measure was selected for its relevance to the desired goal of the CACP program, i.e., shortening and/or preventing ED and hospital utilization. It captures both the initial impact of CP services availability and the effectiveness of the program in meeting the needs of the patient and preventing the return to the ED/hospital subsequent to initial discharge. Planned hospital stays will be excluded from the primary outcome. The secondary outcomes include the proportions of patients experiencing the components of the primary outcome (i.e., percent of patients with unplanned hospitalizations, ED visits, and death), the rates of each component of the primary outcome, the proportion of patients requiring SNF care, as well as patient-reported health-related quality of life (HRQoL) and treatment burden using the patient-reported EQ-5D [19] and PETS [20] measures. For patients in the CACP program, patient satisfaction will also be evaluated. Implementation outcomes, organized by the RE-AIM implementation evaluation framework (Reach, Effectiveness, Adoption, Implementation, and Maintenance), as shown in Table 2, will be ascertained using administrative and EHR data and interviews. Reach and adoption outcomes include metrics for the eligible population, while other implementation outcomes are specific to the intervention group. Additional secondary analyses will assess for the heterogeneity of treatment effects as a function of baseline ED/hospital utilization, source of referral, reason for referral, services delivered, patient demographics (age, sex, rurality, race/ethnicity, limited English proficiency, area-level deprivation), number of CP visits, and duration of CP care. Sensitivity analyses will be performed excluding hospice deaths and utilizing the per-protocol rather than the intention-to-treat approach.

Aim 3 will assess acceptability/satisfaction and perceived sustainability using surveys [21] and interviews with patients, CPs, clinicians and other members of the health care team, and administrators.

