#### Sample size {14}

For aim 1, the sample size will be assessed iteratively during data collection and analysis with the aim of ensuring that the implementation plan is feasible and meets the needs of key user groups. We anticipate up to 25 interviews in the pre-implementation phase for aim 1.

The aim 2 sample size was calculated on the basis of the primary hypothesis. Pilot studies of CP care on days out of ED or hospital in the first 30 days yielded an estimated mean of 27 days in the intervention group. A difference of 2 days was considered clinically important by stakeholders. We have powered this trial to detect a 10% improvement in the primary outcome. To detect a mean difference of 2 days out of ED or hospital at 30 days with a two-sided significance level of 0.05 and a power of 80% with equal allocation to two arms would require 120 patients per group assuming a pooled standard deviation of 5 days. The standard deviation was estimated by assuming the range of measurement will span approximately six standard deviations. Because the primary endpoint is assessed at 30 days and based on the coverage of the EHR, we expect minimal drop-out and missing data. Multiple imputation will be used if more than 20% of patients have missing data on the primary outcome. Aim 3 qualitative inquiry will use a purposeful sampling approach to intentionally select participants who can provide information about their experiences with the program. Based on the past experience of this team, the heterogeneity of expected patient situations, and the scope of this inquiry, we anticipate conducting approximately 25 patient interviews. We anticipate up to 35 clinicians and other stakeholders will also complete aim 3 interviews.

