### Assignment of interventions: allocation

#### Sequence generation {16a}

Individuals will be block randomized 1:1 at the patient level to usual care or to CACP per a computer-generated randomization schedule stratified by source of referral (pre-hospital versus ED versus hospital) and location (Minnesota versus Wisconsin) using blocks of random sizes.

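### The primary comparison is an unadjusted t test, although the plan already intends to use a plausible prognostic baseline measure (prior ED/hospital utilization); some precision is given up, by an unknown and possibly small amount

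*Protocol article*

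**What the plan says.** All places are in the Protocol article.

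- **Primary analysis** (Statistical methods for primary and secondary outcomes {20a}, Aim 2). The contrast is a difference in means: "The mean number of days out of the ED or hospital for the intervention group will be compared to that of the control arm". The method is also fixed: "Statistical significance, and a two-sided confidence interval for the difference between arms, will be assessed by using the two-sample" t test. If the bootstrap distribution of the mean difference is too far from normal, a rank method takes over: "The Hodges-Lehman shift estimator for the Wilcoxon rank-sum test will be used if the absolute value of the skew" or excess kurtosis passes 1.5. Neither method includes a covariate.
- **Baseline utilization** (Outcomes {12}). It is named once, as a possible effect modifier: "Additional secondary analyses will assess for the heterogeneity of treatment effects as a function of baseline ED/hospital utilization", followed by a list of other factors.
- **Covariates** ({20a}, directly after the sensitivity analyses). "The impact of covariates will be assessed by using multiple linear regression or multiple logistic regression". No covariate is named, and the sentence does not replace the t test as the source of the primary result.
- **Randomization** (Sequence generation {16a}). Allocation is "stratified by source of referral (pre-hospital versus ED versus hospital) and location (Minnesota versus Wisconsin"). Neither factor enters the primary test.
- **Sample size** (Sample size {14}). The target is stated as "To detect a mean difference of 2 days out of ED or hospital at 30 days", with two-sided alpha 0.05, 80% power, SD 5 days and 120 patients per group. No covariate adjustment is assumed.

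**The concern.** Past use of acute care is a plausible predictor of later use, and the outcome counts days free of acute care. The plan regards prior utilization as important enough to examine for effect modification, and it takes utilization outcomes from the EHR, where it expects high completeness. Yet the variable is not used where it could narrow the primary interval.

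At stake is the width of the headline confidence interval and the power of the primary test. If adjusted and unadjusted results differ, the plan makes the unadjusted one the primary result. The adjusted one would come from a model whose covariates this document has not fixed.

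**Working it through.** **Inputs.** From Sample size {14}: difference 2 days, SD 5 days, two-sided alpha 0.05, power 80%, 120 per group. Assumed, because the documents do not give it: the correlation r between baseline utilization and the outcome, taken from 0 to 0.5.

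**Step 1: the plan's own figure.** Normal approximation: n per arm = 2 × SD² × (1.960 + 0.842)² / difference² = 2 × 25 × 7.85 / 4 = 98.1, rounded up to 99. The exact t calculation gives 99.08, so 100. The stated 120 is not reproduced; it would fit an inflation of about 20% (100 × 1.2) that the article does not state. That is a separate matter. Here it means only that 120 per arm gives more than 80% power on the plan's inputs.

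**Step 2: unadjusted power at 120 per arm.** Standard error = 5 × √(2/120) = 0.645 days. Noncentrality = 2 / 0.645 = 3.10. Noncentral t power is 87.0%.

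**Step 3: adjustment for one baseline covariate.** Residual SD = 5 × √(1 − r²). The variance of the arm difference falls by r². The equivalent unadjusted size is 120 / (1 − r²) per arm. The half-width is 1.96 × residual SD × √(2/120).

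| Assumed r | Residual SD | Variance cut | Power at 120 per arm | 95% CI half-width (days) | Equivalent unadjusted n per arm |
|---|---|---|---|---|---|
| 0 | 5.00 | 0% | 87.0% | 1.27 | 120 |
| 0.2 | 4.90 | 4% | 88.3% | 1.24 | 125 |
| 0.3 | 4.77 | 9% | 89.9% | 1.21 | 132 |
| 0.4 | 4.58 | 16% | 92.0% | 1.16 | 143 |
| 0.5 | 4.33 | 25% | 94.6% | 1.10 | 160 |

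The gain reaches 5 percentage points only at r of about 0.40.

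**Step 4: if the SD is larger than planned.** The SD of 5 was not observed; {14} derives it by treating the range as about six SDs. With an SD of 6 (an assumption made here), unadjusted power at 120 per arm is 73.0%. It becomes 76.9% at r = 0.3, 80.1% at 0.4 and 84.4% at 0.5. The gain in points is larger where power is shorter.

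**Limit of the table.** It uses a single covariate. With referral source and location also in the model, the further gain from utilization depends on its correlation with the outcome given those factors, which is also unknown.

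**The case against.** The strongest reply is that the plan has chosen a valid analysis and the rest is preference. After 1:1 randomization the unadjusted difference in means is unbiased, and its interval already allows for chance imbalance in prior utilization. A reader might infer that the primary test is biased, or that imbalance makes it wrong. The documents do not support either.

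A reader might also infer that baseline utilization is the outcome itself measured before randomization. That is not supported. The article gives it no unit and no look-back, and it is absent from the assessment schedule (Table 3) and from the subgroup list in {20b}. It might be days, visits or a yes/no history. The outcome also includes the rest of the index episode, which earlier utilization may predict only weakly. Patients come from three referral settings with varied indications, so r could well be low. At r = 0.3 the half-width shrinks by only 0.06 day against a 2-day target.

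Nor does the trial look underpowered on its own inputs: 87.0% exceeds the stated 80%.

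The planned covariate regression is a partial answer, since some adjusted result is foreseen and its covariates may be listed in an SAP that is not shown. It does not settle the point, because this document itself names the primary method, and that method is unadjusted.

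Timing is a fair objection too. Recruitment began in January 2022. The study statistician checks hospitalizations, ED visits and deaths weekly and supplies unblinded data to the DSMB. A covariate chosen now by someone who sees arm-level outcomes would be open to challenge.

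**Conclusion.** The point holds as a matter of efficiency. The primary estimate, interval and p-value are unadjusted, while a plausible prognostic baseline measure that the plan already intends to use is kept for secondary work. This is a free or cheap improvement, not the correction of an error.

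On the plan's inputs, power at 120 per arm would rise from 87.0% by 1.3 points at r = 0.2, 2.9 at 0.3 and 7.6 at 0.5. These figures rest on assumed correlations, on the plan's SD of 5 and on a one-covariate model. If r is 0.2 or less, the variance cut is at most 4%. With about 240 patients and few covariates, adjustment is not expected to lose precision of any consequence even if r is near zero. The target remains a difference in mean days, so the 2-day benchmark still applies.

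**What to change.** Make the primary estimate the arm coefficient, with its confidence interval and p-value, from a linear model of days alive out of the ED or hospital on arm, referral source, location and baseline ED/hospital utilization, using robust standard errors.

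Define the utilization covariate once: its unit, and a fixed look-back that ends before the index episode. This should be done before the final analysis, by team members without access to arm-level outcomes, and the date and their blinded status should be recorded.

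Report the unadjusted t test and the Hodges-Lehmann/Wilcoxon analysis as supportive, and state that the skew and kurtosis rule no longer selects the primary method.

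The cost is revised analysis wording, one look-back query of the EHR already in use, and a documented amendment while recruitment is open. No sample size change is needed.

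### The main tests ignore the six randomisation strata, so if the strata predict the outcome, the confidence interval is too wide and some power is lost.

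*Protocol article*

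**What the plan says.** Sequence generation {16a} describes 1:1 block randomisation "stratified by source of referral (pre-hospital versus ED versus hospital) and location (Minnesota versus Wisconsin". Implementation {16c} confirms six strata, each randomised separately with blocks of random size.

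Statistical methods for primary and secondary outcomes {20a}, Aim 2, compares mean days between arms. The p-value and the confidence interval "will be assessed by using the two-sample *t* test". If the bootstrap distribution of the mean difference is too skewed or heavy-tailed, the Wilcoxon rank-sum test with its Hodges-Lehmann shift estimate takes over. Other continuous outcomes follow the same route. For the rest, "Categorical measures will be assessed by using the Pearson chi-square test", or by Fisher's exact test when expected counts are small. The strata enter none of these.

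Two other places come near. The sensitivity-analysis paragraph of {20a} adds that "The impact of covariates will be assessed by using multiple linear regression or multiple logistic regression". Methods for additional analyses {20b} fits a linear model to the primary outcome with arm, one subgroup factor and their interaction. Referral source is one of those factors; location is not listed.

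**The concern.** Blocking within strata forces the arms to be nearly balanced on referral source and location. Differences between strata then contribute almost nothing to the real sampling variance of the treatment difference. The two-sample t test does not know this and leaves between-stratum variance in its standard error. If the strata matter for the outcome, the planned test is conservative, its 95% interval covers more than 95% of the time, and the precision gained by stratifying is not used.

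Referral source is plausibly prognostic. Participant timeline {13} describes different usual-care paths by source: referral to the ED, admission, or staying in hospital. The article names the test and the source of the interval, so this is not a detail left to an unseen analysis plan. The stated analysis does not use the stated design.

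**Working it through.** **Inputs.** All are from Sample size {14}: an effect of 2 days, two-sided alpha 0.05, power 80% and 1:1 allocation. The article states that this "would require 120 patients per group assuming a pooled standard deviation of 5 days". The SD is a total SD, not a within-stratum one: "The standard deviation was estimated by assuming the range of measurement will span approximately six standard deviations", that is 30/6 = 5.

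**The plan's own figure.** n per arm = 2 × (1.960 + 0.842)² × 5² / 2² = 98.1, so 99 (100 by the noncentral t). The stated 120 does not reproduce from these inputs; at 120 per arm power is about 87.3% (87.0% by the t distribution). That gap is a separate matter. I use 120 per arm below because it is the stated size.

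**Assumed quantity.** R² is the share of total outcome variance lying between the six strata. The document gives no value, so the range 0 to 30% is an assumption.

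**Formulas.** Let f = √(1 − R²).

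- The t test's standard error is about 5 × √(2/120) = 0.6455, so the standardised effect is 2/0.6455 = 3.098.
- The true standard error under within-stratum balance is 0.6455 × f.
- Real two-sided alpha of the t test = 2 × P(Z > 1.960/f).
- Excess interval width = 1/f − 1.
- Power, unadjusted = Φ((3.098 − 1.960)/f).
- Power, adjusted for strata = Φ(3.098/f − 1.960).

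Worked case, R² = 10%: f = 0.9487. Alpha = 2 × P(Z > 2.066) = 3.9%. Excess width = 5.4%. Power = Φ(1.200) = 88.5% unadjusted and Φ(1.306) = 90.4% adjusted.

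| Assumed R² | Real alpha | CI too wide by | Power, planned t test | Power, adjusted |
|---|---|---|---|---|
| 0% | 5.0% | 0% | 87.3% | 87.3% |
| 5% | 4.4% | 2.6% | 87.9% | 88.9% |
| 10% | 3.9% | 5.4% | 88.5% | 90.4% |
| 20% | 2.8% | 11.8% | 89.8% | 93.4% |
| 30% | 1.9% | 19.5% | 91.3% | 95.9% |

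**Simulation check.** Six strata of assumed unequal size, random blocks of 2, 4 or 6, N = 240, normal errors, 6,000 runs per setting, with the adjusted model fitting all six strata.

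- Type I error of the t test was 4.9, 4.5, 4.1, 3.6 and 2.1% at R² of 0, 5, 10, 20 and 30%. The adjusted model gave 4.9 to 5.7%.
- Power was 87.6 against 87.5%, 87.5 against 88.4%, 88.1 against 90.3%, 89.2 against 92.7%, and 90.8 against 95.7%.
- The Monte Carlo standard error near 5% is √(0.05 × 0.95/6000) = 0.3 points. The R² = 20% setting ran somewhat high for both methods, which share the same simulated data. A second simulation gave 4.1, 3.8 and 3.0% for the t test at 5, 10 and 20%.

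Direction and approximate size agree with the formulas.

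**The case against.** The strongest reply is that the error is on the safe side and the design target is met. That stands. On the stated effect and SD, the planned test at 120 per arm keeps power above 80% throughout the table, and no estimate is biased. The margin does depend on an SD taken only from range over six. With an assumed SD of 6, the same formulas give about 74% unadjusted against 78% adjusted at R² = 10%, and 76% against 82% at 20%.

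A second reply is that the size rests wholly on an assumed R². That also stands: the effect is nil at zero and about one power point at 5%. A reader might infer that referral source is strongly prognostic, because a hospitalised patient loses days at once and a pre-hospital patient may lose none. The document does not support that strength. Intervention description {11a} expects most usual-care patients to be sent to the ED and admitted or to take an alternative pathway, so controls from every source may lose days. Every enrolled patient must be suitable for care outside hospital, and the pilot mean under the intervention was 27 of 30 days. Nothing is given on location.

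A reader might also carry the table over to the secondary outcomes. No outcome variance by stratum is available for the binary endpoints, EQ-5D or PETS, so only the direction carries over, and only where the strata are prognostic.

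Thirdly, regressions on covariates and a referral-source interaction model are already planned. They will yield some stratum-aware estimates, and the choice of covariates may properly sit in the analysis plan. But neither replaces the test and interval named for the main analysis.

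**Conclusion.** The point holds as one of efficiency and correct coverage. The design stratifies and the named main analyses do not. If 5 to 10% of outcome variance lies between strata, the primary interval is 2.6 to 5.4% too wide and power is about 1 to 2 points lower than it could be. At 20 to 30%, the interval is 11.8 to 19.5% too wide and the loss is about 3.5 to 4.6 points.

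These figures apply to the primary outcome only. They assume 120 per arm, a 2-day effect, a total SD of 5, near balance within strata, and the stated R². One might read the mismatch as making the p-values invalid or the trial underpowered. Neither follows: type I error is at or below 5%, and power stays above the 80% target on the plan's own inputs. It should be corrected because the improvement is free, not because the conclusions are at risk.

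**What to change.** In {20a}, Aim 2:

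- **Primary outcome:** a linear model for days with arm, referral source (three levels) and location (two levels), robust standard errors, and the adjusted mean difference with its 95% confidence interval. Other continuous outcomes follow, since they already use the primary method.
- **Fallback:** a stratified rank test (van Elteren) in place of the unstratified Wilcoxon, with any shift estimate built from within-stratum comparisons.
- **Binary outcomes:** a Mantel-Haenszel risk difference, or a regression with the same two factors.
- **Sensitivity:** keep the unadjusted t, Wilcoxon and chi-square or Fisher tests.

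The cost is a few sentences, settled before outcomes are analysed by arm. Both factors are already in the REDCap randomisation system. The model uses 3 of 238 degrees of freedom (two for source, one for location) and needs no extra patients.
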